### Participants

Individuals aged 60 years and older, which is the definition for the elderly in Brazil [40], with an established diagnosis of unilateral or bilateral knee OA as established by the American College of Rheumatology criteria of 1986, using history, physical examination, and radiographic findings according to the Kellgren-Lawrence radiographic grading, will be recruited [41]. Patients will be recruited from HSP and from all the outpatient clinics belonging to the Federal University of São Paulo. Eligible subjects will have had pain in the knee for a minimum of 6 months, with an average pain score of 4 or more on a 0-10 numeric rating scale (NRS) for pain over that period and during the week prior to the first stimulation session. Following this, the subjects will be required to report a reduction on NRS during the CPM task of less than 10% compared to the pain score before the test.

Exclusion criteria include patients who have any severe acute or chronic uncompensated disease (such as uncontrolled hypertension, diabetes, cardiac issues, heart failure, or chronic obstructive pulmonary disease), history of epilepsy or syncope, contraindications to transcranial brain stimulation (ie, implanted brain medical devices or implanted brain metallic devices), established cognitive impairment, history of fractures in the lower limbs and/or spine in the last 6 months, traumatic brain injury with residual neurological deficits, alcohol abuse within the last 6 months as self-reported, use of carbamazepine within the last 6 months as self-reported, or severe depression (with a score of more than 30 on the Beck Depression Inventory). The principal investigator will obtain informed consent prior to enrolling participants in the study. We expect in this elderly population to have a female-to-male ratio of about 70%:30%.

In order to avoid drop outs, the principal investigator will follow up with all participants by phone during the entire study to remind them of the schedule. Participants and treating physicians will be told that changes in treatment during the study are strongly discouraged and must be reported. In addition, no treatment crossover will be permitted.

### Randomization and Blinding

We will use a computer-generated list to randomize subjects to one of the two treatment arms: active transcranial direct current stimulation (tDCS-a) or sham transcranial direct current stimulation (tDCS-s). The participants will be randomized with a ratio of 1:1 to either group using randomized block sizes (4 and 6) and stratified by severity of pain (less than 7 and 7 or more). The randomization will be concealed in consecutively numbered, sealed opaque envelopes and will be performed by an investigator not involved in the assessments or the recruitment. The participants and investigators who will perform the evaluation will be completely blinded until completion of the study and data processing.

### Intervention

The treatment will be administered for 3 weeks with intervention sessions daily from Monday to Friday for a total of 15 days of electrical stimulation [37]. The participants will not receive cash, reimbursements, food, transportation, or any compensation for their participation in the trial. After the initial assessment and before randomization, the subjects will be informed about the possible sensations with the stimulation and instructed not to reveal the sensation experienced.

Participants will be seated comfortably in an armchair while receiving tDCS. All subjects will receive 20 minutes of either sham or active tDCS, using a pair of 35 cm^2^ surface sponge electrodes soaked with physiologic saline and fixed to the head with elastic bands. The transcranial stimulation will be applied by a constant current device (Soterix 1×1 Low-Intensity Stimulator, Soterix Medical Inc) with an intensity of 2 mA. A gradual current ramp-up and ramp-down with 30-second durations will be used. The anode will be placed over C3/C4 (International 10-20 electroencephalogram system), which corresponds approximately to the location of M1 of the contralateral side to the most affected knee. The cathode electrode will be placed over the contralateral orbital, meaning ipsilateral to the most affected knee. The tDCS will be administered by a physician with specific training is this modality of intervention.

Sham tDCS stimulation will look and feel exactly the same as the active stimulation; however, the stimulator will deliver 2 mA of current for only 30 seconds. This sham stimulation method is frequently used and has been shown to be reliable [42].

**Figure 1 figure1:**
[figure not shown]
Flowchart of the study based on Consolidated Standards of Reporting Trials criteria. tDCS: transcranial direct current stimulation.

### Outcome Measurements

Following determination of participant eligibility and obtaining informed consent, we will collect baseline information about the subjects through a structured interview. Collected data will include sociodemographic information, mood and cognitive evaluation, radiographic data, and clinical history. We will perform all assessments during the baseline visit to obtain data to compare with the follow-up visits. Baseline data will be collected 1 week prior to the beginning of treatment. After 3 weeks of intervention, we will evaluate the participants over the course of 2 months, with 3 follow-up visits during this period (see Figure 1 for flow diagram). These outcome time points were chosen based on tDCS trials to assess early and late effects [27,36,37].

### Primary Outcome

We will analyze pain intensity in the previous 24 hours using the Brief Pain Inventory (BPI); this is a short, self-report questionnaire [43]. The BPI includes 4 items that measure pain intensity (pain right now, pain on average in last 24 hours, worst pain in last 24 hours, and least pain in last 24 hours) using an NRS from 0 (no pain) to 10 (pain as bad as you can imagine). The mean of these 4 pain items will be used as our primary outcome. The BPI also includes 7 items that assess the impact of the pain on functioning using a 0 (no interference) to 10 (complete interference) rating scale, which will be used as a secondary outcome.

### Secondary Outcomes

#### Quality of Life

We will assess health-related quality of life using the 12-Item Short Form Health Survey questionnaire, which comprises 8 domains that include physical functioning, physical role functioning, bodily pain, general health perceptions, vitality, social functioning, emotional role functioning, and mental health [44].

#### Pain Perception

Mechanical detection threshold (MDT) will be assessed using a Von Frey monofilament (VFM) as a mechanical stimulating device to evaluate light touch and pinprick sensation in small cutaneous regions. The investigator will use the smallest weighted monofilament, followed by sequentially larger monofilaments until the participant reports when the light touch sensation is first detected and then until the pinprick sensation is detected. VFM will be applied perpendicular to the skin with the correct amount of force to bow the monofilament for approximately 1.5 seconds. VFM will be applied first to the thenar region, ipsilateral to the most affected knee, and then applied to the most painful knee [45].

Mechanical pain threshold (MPT) will be measured using the same technique used to assess the MDT. However, the subject will be asked to report the smallest monofilament that produces pain. Following this, we will apply the same monofilament on either region 3 times, and the participants will be asked to rate the pain using an NRS; the mean score will then be calculated [45,46].

#### Pressure Pain Threshold

The pressure pain threshold (PPT) will be assessed using a pressure algometer (Commander Echo Algometer, JTECH Medical Industries Inc) that has a 1-cm^2^ rubber probe. The probe will be applied perpendicular to the skin until the subject first reports that the pressure sensation changes to a pain sensation. Participants will be asked to rate the pain using an NRS. The pressure will be applied to exactly the same regions that we will use to assess MDT and MPT [47].

#### Conditioned Pain Modulation

CPM will be measured using cold water as the conditioned stimulus and pressure as the test stimulus to assess endogenous pain modulation. Pressure will be applied using the same device and technique as for the PPT. Participants will be asked to immerse their contralateral hand to the most affected knee in a cold water bath maintained at 10^o^C for approximately 1 minute. In the last 30 seconds, the test stimulus will be applied following the PPT procedure [15-17].

We will calculate the percentage change in pain scores following CPM, a measurement we will call CPM-P, and the change in the PPT after the CPM that we will call CPM-PPT. Both of them will be calculated using the following formula: (post-CPM trial score − pre-CPM trial score / pre-CPM trial score) × 100. For CPM-P, a negative score will indicate pain inhibition after the conditioning stimulus. For CPM-PPT, a positive score will indicate pain inhibition after the conditioning stimulus.

#### Physical Functioning

The Western Ontario and McMaster Universities Osteoarthritis Index is a valid and reliable instrument commonly used to assess pain and disability in studies of knee OA. The questionnaire includes 3 subscales to assess pain, perceived disability, and joint stiffness. The total score ranges from 0 to 96, with higher values indicating greater physical impairment [48].

The Lequesne Algofunctional Index is a questionnaire that assesses 3 components of severity of OA: pain, maximum walking distance, and activities of daily living. The total score ranges from 0 to 24, with higher values indicating greater physical impairment [49].

The timed up and go test is a reliable and practical test to evaluate functional capacity commonly used in research studying elderly populations, especially because of its capacity to assess risk of falls and gait function. Subjects will be asked to get up from a chair in which they were fully supported, walk 3 meters, turn around, return by the same route, and sit back down on the chair with their back supported. We will measure the time required to complete the test. The test will be performed twice, and the lowest score will be recorded [50-52].

The one leg stance test is used to evaluate postural balance. The participants will be asked to stand unsupported on one foot while looking straight ahead with their hands on hips. We will measure the time the subject is able to maintain balance until the contralateral foot touches the ground. The test will be performed twice, and the highest score will be recorded [52,53].

#### Pain Impact on Functioning

The mean of the 7 BPI interference items (general activity, mood, walking ability, normal work, relations with other people, sleep, enjoyment of life) will be used to assess the pain impact on functioning.

#### Patient Global Assessment

We will analyze the patient’s global assessment on how the intervention affects the patient’s status using a 0-100 visual analog scale (VAS) scale [54].

#### Adverse Effects

At each stimulation session and at all follow-ups, participants will be administered a questionnaire to evaluate potential adverse effects of stimulation on a 5-point scale. The main potential adverse effects include headache, neck and scalp pain, tingling, sleepiness, and acute mood change. If any side effect is reported, its potential relationship with the intervention will be assessed [55].

To assess the safety of tDCS, we will analyze the mood and cognition of the subjects at each stimulation session and at all follow-ups. Mood will be assessed with a 0-100 VAS scale by asking the subject to rate their own emotions including anxiety, depression, stress, and sleepiness. Cognition will be analyzed using the Mini-Mental State Examination, a brief screening of cognitive abilities [56].

### Sample Size and Data Analysis

The sample size was estimated using the minimal clinically important difference (20% reduction from the baseline) in the outcome of pain intensity measured by the NRS as a parameter. The effect size and the probability of error type I (alpha) and type II (beta) were 0.59, .05, and .2, respectively. According to the sample calculation, that total size would be 94 participants. We will increase the sample size by 10% to account for dropouts and other unexpected factors. Thus, the final sample size is 104 subjects.

All analyses will be conducted according to the principle of intention-to-treat (ITT) using a regression-based single imputation method. The ITT population will include all randomized subjects. We will perform an additional sensitivity analysis in which we will use the method of multiple imputation. Initially, the baseline characteristics between sham and tDCS groups will be tested using Student *t* tests; to analyze our primary outcome, which is pain intensity measured by BPI, we will adopt a mixed analysis of variance model in which the dependent variable will be the outcome (BPI) and the independent variables will be group (tDCS-a or tDCS-s), time (baseline and after treatment and follow-up), and the interaction group time. Secondary analyses will be conducted in an exploratory manner (no correction for multiple comparisons). Similar analysis will be conducted for the adverse effects measuring continuous outcomes, and for the categorical outcomes, we will use Fisher exact tests. In both cases, for the safety analysis, we will use uncorrected *P* values to increase the likelihood of detecting detrimental adverse effects.

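### The imputation rule covers all analyses, so as written it fills in adverse-effect scores for stimulation sessions that were never delivered

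*Protocol article*

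**What the plan says.** Three statements in the protocol article, Sample Size and Data Analysis, set the rule:

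- Scope and method: "All analyses will be conducted according to the principle of intention-to-treat (ITT) using a regression-based single imputation method".
- Population: "The ITT population will include all randomized subjects".
- Sensitivity analysis: "We will perform an additional sensitivity analysis in which we will use the method of multiple imputation".

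The same paragraph brings safety under this approach: "Similar analysis will be conducted for the adverse effects measuring continuous outcomes, and for the categorical outcomes, we will use Fisher exact tests". The one adaptation it makes for safety is to the P values: "for the safety analysis, we will use uncorrected *P* values to increase the likelihood of detecting detrimental adverse effects".

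The Adverse Effects section gives the data schedule: "At each stimulation session and at all follow-ups, participants will be administered a questionnaire to evaluate potential adverse effects of stimulation on a 5-point scale". Mood ratings and the Mini-Mental State Examination follow the same schedule. The Intervention section plans 15 sessions over three weeks.

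**The concern.** The questionnaire asks about effects of stimulation. If a session was not given, there was no stimulation to cause an effect. The score for that session is undefined, which is different from a value that exists but was not observed. A rule that imputes for all analyses in everyone randomized makes no such distinction. It fills the empty session records of a participant who stops early, and it gives a complete set of tolerability scores to someone randomized but never stimulated.

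What is at stake is the comparison of continuous adverse-effect scores between arms. Safety is a listed secondary outcome, and the Discussion gives limited experience in elderly patients as a reason to study it. Part of that comparison would rest on values with no meaning, in an analysis whose stated purpose is "to increase the likelihood of detecting detrimental adverse effects". Replacing single with multiple imputation does not help, because it too generates values for sessions that did not occur.

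**Working it through.** **Reading the text.** The scope is all analyses, the population is everyone randomized, continuous adverse-effect outcomes get a similar analysis, and scores are collected at each session. No sentence limits the scope to efficacy. Together these lead to imputed adverse-effect scores for undelivered sessions. This is what the general rule implies; the article does not describe it as a separate step.

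**The plan's own figures.** The article gives no figure on this point. Its sample size is used below only to set the arm size. A two-sided two-sample t-test with effect size 0.59, alpha .05 and power .80 needs 46.08, so 47 per arm and 94 in total, as stated (two-sided is assumed). Then 94 × 1.10 = 103.4, so 104, as stated. At 1:1 allocation this is 104 / 2 = 52 per arm, or 52 × 15 = 780 planned session records per arm.

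**Illustration. All inputs below are assumed except 52 per arm and 15 sessions.**

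- Session scores are confined to 0–4: 1.0 + 0.3 × (active arm) + a participant effect (SD 0.6) + session noise (SD 0.6).
- The active participants with the highest score in sessions 1–3 stop after session 3. A stopping share of 5% is 3 of 52 and leaves 3 × 12 = 36 of 780 records empty (4.6%). A share of 10% is 5 of 52 and leaves 5 × 12 = 60 of 780 empty (7.7%).
- Each participant's scores are averaged and the arms compared by t-test, with 2,000 runs per setting. The rejection rate is the share of runs with P < .05.

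| Handling of sessions after the stop | Difference, 5% stop | Rejection rate, 5% stop | Difference, 10% stop | Rejection rate, 10% stop |
|---|---|---|---|---|
| Reference: all sessions given and observed | 0.27 | 0.67–0.69 | 0.27 | 0.67–0.68 |
| Imputed from pooled mean | 0.22 | 0.56 | 0.20 | 0.49 |
| Imputed from arm only | 0.23 | 0.57 | 0.21 | 0.51 |
| Imputed from arm and own earlier scores | 0.27 | 0.69 | 0.27 | 0.68 |
| Observed sessions only | 0.29 | 0.70–0.72 | 0.29 | 0.72–0.73 |

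**Dilution** = (reference − imputed) / reference, using unrounded differences:

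- 5% stop: pooled (0.272 − 0.224) / 0.272 = 18%; arm only (0.274 − 0.231) / 0.274 = 16%.
- 10% stop: pooled (0.273 − 0.198) / 0.273 = 27%; arm only (0.273 − 0.206) / 0.273 = 25%.
- Own earlier scores included: essentially none at either share.

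**Any occurrence.** The difference between arms in the share of participants with any score of 2.5 or more was about 0.155 in every setting. Imputation changed it by no more than 0.001, because recorded scores are not overwritten.

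**Limits of the illustration.** The reference row assumes that stoppers would have continued, which is itself hypothetical. The observed-only row is slightly higher because stoppers contribute only three sessions, on which they were selected for high scores. No run was made with equal arms, so the effect of understated variance on false positives is not quantified.

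**The case against.** The strongest reply is that the article never says scores are predicted for undelivered sessions. The time factor in its mixed model is baseline, after treatment and follow-up, with no 15-level session factor, and the article does not say adverse-effect scores are modelled session by session. This stands in part. The number of records imputed is unknown, and the counts of 36 and 60 describe one possible analysis. It does not remove the point, because the rule as stated still covers adverse-effect scores and nothing exempts them.

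A reader might infer that the safety signal is smoothed away, or that the result is bound to favour good tolerability. The documents do not support either reading:

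- Imputation fills gaps and leaves recorded scores in place. Fisher tests on any occurrence are unaffected, reported side effects are still assessed for their relation to the intervention, and nothing in the rule removes a discontinuation from the report.
- Dilution of the mean score depends on an imputation model that is not given. It was absent in the illustration when the participant's own earlier scores were used.
- Single imputation understates variance, which pushes P values down. The direction of the error is therefore not fixed.

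A reader might also extend the point to mood and cognition. That does not hold. Both exist whether or not stimulation is given, and values missing at scheduled follow-ups are ordinary missing data.

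Finally, a condensed article may leave the definition of a safety population to a full protocol or analysis plan that is not shown. Agreed: that absence is not criticised here. The fault lies in what is stated, because a later document that exempted safety data would contradict a rule written for all analyses.

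**Conclusion.** The point holds as a fault of scope. Read literally, the stated rule imputes adverse-effect scores for sessions that were not delivered. Those values are undefined under single and multiple imputation alike, and producing them sits badly with the section's stated aim of detecting harm.

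The consequence is confined to the continuous adverse-effect comparison and its size is conditional. Under the assumed inputs, dilution was 16–18% with 5% of the active arm stopping and 25–27% with 10%, if the model ignores the participant's own earlier scores. It was about nil if the model uses them. The actual stopping rate, the imputation model and the unit of analysis are not given, so no bias of known size or direction is established. The primary pain analysis and the sample size are not affected by this point. It is worth correcting because the rule is wrong in principle for these data and the correction is cheap.

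**What to change.** Limit the sentence on intention-to-treat and imputation to efficacy outcomes. Add that adverse effects will be analysed on observed data, without imputation, in participants who received at least one session. Use per-participant summaries: any occurrence, and worst score while on stimulation. Compare the number in each arm who stop sessions because of an adverse effect by Fisher exact test.

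To show the reach of that last comparison (assumed counts, 52 per arm): 5 stops against 0 gives P = .057, and 6 against 0 gives P = .027. The counts should therefore be reported by arm whatever the P value.

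The cost is about two sentences and no new data. The downside is small: per-participant summaries carry less session-by-session detail, and participants randomized but never stimulated leave the adverse-effect tables.

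### Single regression imputation is the primary missing-data method: depending on whether arm is in the imputation model, it either raises the type I error moderately or attenuates the treatment effect

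*Protocol article*

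**What the plan says.** All the relevant statements are in the protocol article, Sample Size and Data Analysis.

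- Primary handling of missing data: "All analyses will be conducted according to the principle of intention-to-treat (ITT) using a regression-based single imputation method".
- Analysis population: "The ITT population will include all randomized subjects". Every participant with missing visits therefore has values filled in.
- Primary model: a mixed ANOVA of the BPI pain score on group, time and their interaction.
- Role of multiple imputation: "We will perform an additional sensitivity analysis in which we will use the method of multiple imputation".
- Planning figures: "The effect size and the probability of error type I (alpha) and type II (beta) were 0.59, .05, and .2, respectively", giving 94 participants. Then: "We will increase the sample size by 10% to account for dropouts and other unexpected factors" and "Thus, the final sample size is 104 subjects".

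The section describes no variance correction for the imputed values. It does not say which predictors enter the imputation regression, in particular whether arm is one, or whether a random residual is added to the prediction.

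**The concern.** A mixed ANOVA on a completed data set cannot tell a measured score from a predicted one. It counts degrees of freedom as though nobody had left and adds nothing for the uncertainty of the imputed values. If the prediction is deterministic, the filled-in points also lie on the regression surface and reduce the residual variance. When the imputation regression contains arm, the standard error of the treatment contrast is then too small and a nominal 5% test rejects too often.

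When the regression omits arm, missing scores in both groups are predicted from one common equation. This pulls the group means together and dilutes a real effect.

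The trial's one confirmatory comparison, planned at alpha .05, would rest on one of these two analyses. The method without the fault is in the plan but has the subordinate role. If the two disagree near the 5% boundary, the plan as written gives precedence to the weaker one.

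**Working it through.** **1. The plan's own sample size.** Inputs from Sample Size and Data Analysis: d = 0.59, alpha .05 (two-sided assumed; the article does not say), power 1 − .2 = .80. Allocation 1:1 from Randomization and Blinding.

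- Normal approximation: n per arm = 2(1.960 + 0.842)² / 0.59² = 2 × 7.85 / 0.348 ≈ 45.1, so 46 per arm (92 in total).
- Solution based on the t distribution: 46.08, so 47 per arm, **94 in total**. This matches the plan.
- Allowance: 94 × 1.1 = 103.4, so **104**. This matches the plan. (Dividing instead, 94 / 0.9 = 104.4, would give 105.)

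The sample size reproduces and is not at issue here.

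**2. Simulation set-up.** 104 participants, 52 per arm, five time points (baseline, end of treatment, and 2, 4 and 8 weeks later). The following are assumptions, not in the article: equal correlation between all visits (0.5 in the main runs) and monotone dropout completely at random, with the first missed visit equally likely to be any of the four post-baseline visits. At 10% dropout, the expected share missing is thus 2.5%, 5%, 7.5% and 10% at the four visits in turn. Missing scores were filled visit by visit by regression on all earlier visits, with or without arm, and with arm also with a random residual. Two tests were applied to the completed data: the group-by-time F test, and the between-arm difference in change from baseline to week 8. Each null scenario had 8,000 trials, so the Monte Carlo standard error near 5% is √(0.05 × 0.95 / 8000) ≈ 0.24 percentage points.

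**3. Arm in the imputation regression, no true effect** (deterministic / with random residual).

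| Dropout | Group-by-time error | Week-8 error | Week-8 mean SE ÷ true SD |
|---|---|---|---|
| 5% | 6.2% / 6.4% | 5.7% / 5.9% | 0.963 / 0.965 |
| 10% | 8.5% / 8.0% | 7.1% / 6.6% | 0.924 / 0.930 |
| 20% | 11.9% / 11.0% | 8.8% / 8.6% | 0.860 / 0.875 |

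A repeat with 3,000 trials per cell gave somewhat lower values at 10% dropout: 7.3-7.5% for the F test and 6.1-6.4% for week 8, with the SE 5-8% too small. With correlations from 0.3 to 0.7 at 10% dropout, the F-test error stays at about 7-9%. Adding a random residual does not cure the problem.

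**4. Arm left out (deterministic).** With no true effect, the F-test error is 4.9%, 5.5% and 5.0% at 5%, 10% and 20% dropout; for week 8 it is 5.1%, 5.3% and 4.9%. SE ratios are 0.993-0.997. With a true effect of 0.59 and 10% dropout (3,000 trials), the mean week-8 estimate is 0.550, against 0.584-0.585 when arm is included. That is a loss of about 1 − 0.550/0.585 = 6%. Repeat runs gave about 0.56 at 10% dropout and about 0.52 at 20%. The loss is partial because earlier post-baseline scores, where observed, carry some of the arm difference.

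**5. Multiple imputation as primary** (arm included, 10 imputations, Rubin's rules, week-8 contrast). The type I error is 5.1%, 5.2% and 4.6% at 5%, 10% and 20% dropout, with SE ratios of 1.00, 1.00 and 1.01. At d = 0.59 and 10% dropout the mean estimate is 0.585 and power about 80%. Single imputation with arm shows an apparent 82-84%, and the difference comes from the understated standard error.

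**The case against.** The strongest reply is that the inflated error rate depends on a choice the article never states. If arm is not a predictor, the test holds its level, and the remaining fault is mild and conservative. This stands, and it rules out the flat statement that the 5% level is exceeded. It does not rescue the method, because the alternative is an attenuated effect estimate.

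Three further points count in the plan's favour. The 10% allowance covers dropouts together with other unexpected factors, and Participants describes phone follow-up to limit losses, so 20% dropout is a what-if and not the plan's expectation. At 5% dropout with arm included, the excess is small (about 5.5-6.4%). And the planned multiple imputation would expose missing imputation uncertainty if the two analyses diverged. All three limit the size of the problem. None justifies letting the weaker method carry the primary conclusion.

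A reader might also infer, from the words covering all analyses, that adverse effects will be imputed from participants who stayed and harm thereby understated. The article does not support this. It describes the safety analysis separately and nowhere says that adverse effects are imputed. Under Adverse Effects they are collected at each stimulation session and every follow-up, so what happened at sessions attended before stopping is observed.

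Nor is the lack of a sensitivity analysis that departs from missing-at-random a fault of this article. That detail is commonly left to an analysis plan, which is not shown here.

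**Conclusion.** The point holds in conditional form. The article fixes single regression imputation as primary, and both readings of it are unsound:

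- **Arm included:** type I error of about 7-8.5% for the group-by-time test and about 6-7% for the week-8 contrast at 10% dropout, with the SE about 5-8% too small. At 20% dropout the errors would be about 11-12% and 8.5-9%.
- **Arm excluded:** error near 5%, but a true 0.59 estimated at about 0.55-0.56 at 10% dropout.

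The figures rest on monotone dropout completely at random and a within-patient correlation of about 0.5; other dropout patterns would change them. At the planned allowance the fault is moderate, and a sound method is already in the plan. It should be fixed, but it does not by itself invalidate the trial.

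**What to change.** Exchange the roles of the two methods already planned. Make multiple imputation primary, with arm in the imputation model and estimates combined by Rubin's rules. Alternatively, fit a likelihood-based mixed model to all observed data from all randomised participants, which needs no imputation. Keep single imputation at most as a sensitivity analysis, and if it is kept, state its predictors and whether a residual is added.

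The cost is a change of wording, a little programming and slightly wider intervals. No further participants, visits or data are needed: with multiple imputation as primary, power at 10% dropout was about 80%. The Results section reports 25 participants included and 10 completed at publication, so the change could be made and documented well before unblinding.

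### The primary model uses baseline pain only as a level of time and omits the randomisation stratum: valid, but less precise than adjusting for baseline

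*Protocol article*

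**What the plan says.** Under Sample Size and Data Analysis, the protocol article states for the primary outcome that "we will adopt a mixed analysis of variance model in which the dependent variable will be the outcome (BPI"). It then names the independent variables: group, time and the group-by-time interaction. Baseline is listed as one of the levels of time. No covariate is named. The list reads as complete, so this is a stated choice and not a detail left open.

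Under Randomization and Blinding, allocation is 1:1 in blocks and "stratified by severity of pain (less than 7 and 7 or more"). No analysis text uses that factor.

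The same analysis section opens with "Initially, the baseline characteristics between sham and tDCS groups will be tested using Student" *t* tests.

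Under Outcome Measurements, every assessment is made at the baseline visit, so a pre-treatment BPI pain score will exist for each participant.

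For the sample size, the article takes the "minimal clinically important difference (20% reduction from the baseline) in the outcome of pain intensity measured by the NRS as a parameter", and states: "The effect size and the probability of error type I (alpha) and type II (beta) were 0.59, .05, and .2, respectively". It gives no SD and no correlation between baseline and later scores.

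**The concern.** When baseline is a level of the repeated factor, the interaction contrast between baseline and a later visit compares mean change between arms. That gives the baseline score a fixed weight of one. Regression on baseline lets the data set the weight, and its variance is smaller whenever the correlation is below 1. The group main effect does not help: it averages the pre-treatment score, which treatment cannot have affected, into the comparison.

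Leaving out the stratum is a second departure from the design. If the stratifier tracks baseline BPI, stratified allocation has already removed some between-arm variation, and a model that ignores the stratum does not credit this in its standard error.

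At stake is a wider confidence interval for the primary effect, and lower power, than the collected data allow.

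**Working it through.** **Reproducing the plan's figure.** Inputs from Sample Size and Data Analysis: effect size 0.59, alpha 0.05, beta 0.2, total 94, increase 10%, final 104. Sidedness is not stated. A two-sided two-sample t test with 1:1 allocation needs 47 per arm, total 94, with power 80.8%. One-sided testing gives 36 per arm by the normal approximation, which does not fit. For dropout, 94 × 1.10 = 103.4, rounded up to 104. The sample size therefore reproduces as a plain two-group comparison of means.

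**Variance of one contrast** (a single post-treatment visit, in units of the outcome variance, equal variances over time):

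- change from baseline: 2(1 − rho)
- adjusted for baseline (ANCOVA): 1 − rho²
- ratio: (1 − rho²) / [2(1 − rho)] = (1 + rho)/2

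Rho is an assumption, shown over a range. Power is from the noncentral t distribution at 47 per arm, with 0.59 taken on the raw outcome SD.

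| rho | change variance | ANCOVA variance | ratio | power, planned | power, ANCOVA | N for 80%, planned | N for 80%, ANCOVA |
|---|---|---|---|---|---|---|---|
| 0.3 | 1.40 | 0.91 | 0.65 | 66.7% | 84.3% | 130 | 86 |
| 0.5 | 1.00 | 0.75 | 0.75 | 80.8% | 90.4% | 94 | 70 |
| 0.7 | 0.60 | 0.51 | 0.85 | 95.5% | 97.7% | 58 | 50 |

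In patients, ANCOVA needs 1 − 0.65, 1 − 0.75 and 1 − 0.85, that is 35%, 25% and 15% fewer. Seen from the other side, the planned contrast needs 1/0.65 = 1.54, 1/0.75 = 1.33 and 1/0.85 = 1.18 times as many, that is 54%, 33% and 18% more.

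Below rho 0.5 the change variance 2(1 − rho) exceeds 1. On the raw-SD reading, the planned contrast is then less precise than the post-treatment comparison that yields 94.

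**If 0.59 is on the SD of change.** Planned power is 80.8% at every rho. The standardised effect under ANCOVA becomes 0.59/√0.65 = 0.73, 0.59/√0.75 = 0.68 and 0.59/√0.85 = 0.64, so there is still a gain.

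**The stratum.** This was simulated with 3,000 runs, N = 94, five time points, equal correlations, and blocked randomisation stratified on baseline BPI split in two. That split is an assumption, since the article does not say which pain score defines the stratum.

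| rho | change: model SE | change: empirical SE | change: type I error | power, change | power, change + stratum | power, ANCOVA | power, ANCOVA + stratum |
|---|---|---|---|---|---|---|---|
| 0.3 | 0.243 | 0.216 | 0.027 | 67.6% | 76.7% | 83.4% | 83.0% |
| 0.5 | 0.206 | 0.187 | 0.034 | 83.1% | 87.4% | 91.0% | 91.0% |
| 0.7 | 0.159 | 0.153 | 0.037 | 95.6% | 96.6% | 97.1% | 97.0% |

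Without the stratum, the planned contrast reports too large a standard error and tests conservatively. So when the stratifier follows baseline BPI closely, part of the loss is an overstated standard error and not true noise. At rho 0.3 the empirical variances differ by (0.2162/0.1964)² = 1.21, against 1.54 from the formula. Power is lost either way. Once continuous baseline is in the model, the stratum adds nothing measurable.

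**The case against.** A group-by-time mixed ANOVA is a legitimate, prespecified analysis, and choosing a more efficient valid model is an improvement and not the repair of an error. That stands. A reader might infer bias or an inflated type I error; the documents and the simulation support neither, and the planned test is if anything conservative. A reader might also infer that 94 or 104 is miscalculated; both figures reproduce.

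The size of the loss rests on quantities that the article does not give. This also stands. The lower planned powers need a low rho and 0.59 on the raw SD. The article's reference to a reduction from baseline can equally be read on the change scale, and then planned power stays at about 81%. At rho 0.7 the gain is about two points. The calculation also takes one contrast, while the plan names none; the omnibus interaction test gave 70.3%, 85.6% and 98.0% at rho 0.3, 0.5 and 0.7. What survives is the direction: the variance ratio is below 1 for every rho below 1, on either scaling.

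It is tempting to read the baseline t tests as deciding whether to adjust. The article does not say so: it attaches no consequence to them, and the model terms are fixed whatever they show. Nor is baseline pain ignored, since the change contrast subtracts it. The tests cost no precision. They are merely uninformative, because randomisation already makes their null hypothesis true.

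**Conclusion.** The point holds as one of efficiency. The primary model as stated uses baseline BPI less well than it could and leaves out the factor used to stratify randomisation. At assumed rho of 0.3 to 0.7, adjustment saves about 35% to 15% of patients for the same model-based precision. The gain for one contrast at 47 per arm runs from about 18 percentage points of power (84.3 − 66.7) down to about 2 (97.7 − 95.5), if 0.59 is on the raw SD.

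A reader might conclude that the trial is underpowered. The documents do not support this: it would need both a rho below 0.5 and the raw-SD reading, and neither is stated.

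Nearly all the gain comes from continuous baseline BPI. The stratum belongs in the model to match the design, not for further precision. The change is worth making but is not essential to the validity of the trial.

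**What to change.** Before unblinding, by a documented amendment:

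- Model post-baseline BPI on group, time, group × time, baseline BPI, baseline BPI × time, and the randomisation stratum (below 7, or 7 and above). Take baseline out of the outcome vector.
- Do the same for continuous secondary outcomes that have a pre-treatment value. This excludes the Patient Global Assessment, which rates the effect of the intervention and so has no natural baseline.
- Replace the baseline t tests with a descriptive table by arm.

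If the planned model were kept, the stratum would have to enter together with its interaction with time. With complete data, which single imputation produces, a stratum main effect cancels from the group-by-time contrast.

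No new data are needed. The cost is a change to the primary model during enrolment: the Results section reports 25 participants included and 10 completed. The amendment should therefore be dated and should state that it was made without sight of outcomes by arm.
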